**Methods:**

Effectiveness and health-economic outcomes are evaluated in a prospective, quasi-experimental, controlled study under real-world conditions. The intervention group includes patients from 20 participating practices; the control group is matched using routine claims data. The primary endpoint is the number of ambulatory care–sensitive emergency cases after 12 months, analyzed intention-to-treat. Secondary outcomes include healthcare utilization, mortality, continuity, and coordination of care. Statistical analyses will account for confounding and clustering at practice and patient level. The health economic evaluation will estimate incremental cost-effectiveness ratios based on ambulatory and total healthcare costs. A parallel process evaluation uses longitudinal mixed-methods. It comprises interviews, activity logs and focus groups, and surveys among patients, their relatives, practice teams and collaborators. Key aspects assessed include implementation facilitators and barriers, organizational development and interprofessional collaboration, nurse role development, and patient quality of life and treatment satisfaction.

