### Sample size calculation

For the sample size and power calculation, a baseline rate of 0.20 ASE per patient per year is assumed. In the general population, ASE rates range between 4% and 8% [22]. As the study population consists of patients with chronic conditions selected based on clinical judgement and expected to benefit from enhanced care, a higher baseline rate is expected. Based on published evidence suggesting a 20–40% reduction in ASEs through improved ambulatory care [23], a conservative effect size of 15% is applied.

The study follows a parallel cluster design with 20 practices per arm and approximately 112 patients per practice. This accounts for an anticipated dropout of 20% at practice level and 10% at patient level. The design includes 12 months of pre- and 12 months of post-intervention observation [24]. An intra-cluster correlation coefficient (ICC) of 0.01 is used. Under these assumptions and a two-sided alpha of 5%, the study achieves a statistical power of 82% to detect a 15% reduction in ASE rates.

The PE within PRIMA does not assess a primary endpoint of the study. Therefore, no separate sample size calculation was required for the PE. Instead, the sample size of the PE is determined by the total population of all participant groups included in the PRIMA study and by the methodological approach chosen within the PE sub-projects. For the questionnaire-based quantitative PE, all patients included in the main study as well as all staff members of the participating practices will be included (estimated n = 2,000). To ensure sufficient thematic breadth regarding the research questions – while simultaneously aiming for thematic saturation – a total of 4 practices will be included in the qualitative case studies, leading to about 60 individual interviews (30–60 minutes) with patients, relatives, and practice staff, along with approximately 16 qualitative activity logs. In addition, 4–5 cross-site focus groups (approximately 120 minutes each) with members of the PRIMA teams and stakeholders at interface levels (e.g., care support centers) are planned.

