#### Effectiveness evaluation.

The primary endpoint (number of ASE after 12 months) will be analyzed according to the ITT principle. The ITT population of the IG comprises all patients enrolled in the NCM by the end of the nine-month recruitment period, receiving at least 12 months of care. The smallest unit of analysis is the individual patient, as outcomes are assessed at patient level. In a baseline analysis, sociodemographic and clinical characteristics of the IG will be compared with those of the matched CG to assess the effectiveness of the matching procedure and identify potential determinants of the study endpoints [34,35]. The significance of the differences will be tested using linear mixed models for continuous variables with normal distribution, logistic models for binary variables, and the chi-square test and Fisher’s test for categorical variables. Subsequently, the rate of ASE in the IG and CG will be analyzed using multi-level regression models with patients nested within practices to account for the hierarchical structure of the data [36]. As a sensitivity analysis, models with cluster-robust standard errors at the practice level will be estimated. Relevant covariates identified in the initial analyses will be included in adjusted regression models [37].

Continuous secondary endpoints, including healthcare costs, will be analyzed using adjusted mixed linear models. Mortality will be assessed using survival analyses, while binary outcomes will be analyzed using generalized linear mixed models. Covariates will be selected analogously to the primary analysis. Extensive sensitivity analyses are planned to assess the robustness of the evaluation parameters. The choice between matched datasets derived from KVBW or AOK-BW routine data will depend on the respective endpoint as specified in Table 2. Statistical significance will be defined as a two-sided p-value <0.05. Where relevant, 95% confidence intervals are provided.

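### Chi-square and Fisher tests of baseline balance ignore practice clustering and matching, so the p-values used to judge the match and pick covariates are miscalibrated

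*Protocol article*

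**What the plan says.** Under Effectiveness evaluation, the protocol article plans a baseline comparison of the intervention group with the matched control group. Its stated purpose is "to assess the effectiveness of the matching procedure and identify potential determinants of the study endpoints". The significance of differences is tested by variable type:

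- continuous variables: "linear mixed models for continuous variables with normal distribution"
- binary variables: "logistic models for binary variables"
- categorical variables: "the chi-square test and Fisher’s test for categorical variables"

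The results are carried forward: "Relevant covariates identified in the initial analyses will be included in adjusted regression models". Covariates for the secondary endpoints are selected in the same way. For the outcome itself, the section specifies "multi-level regression models with patients nested within practices to account for the hierarchical structure of the data", with cluster-robust standard errors as a sensitivity analysis.

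The abstract says that "Statistical analyses will account for confounding and clustering at practice and patient level". The Sample size calculation plans 20 practices per arm with about 112 patients each and states: "An intra-cluster correlation coefficient (ICC) of 0.01 is used". That ICC belongs to the power calculation for the ASE rate. No ICC is given for any baseline characteristic.

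**The concern.** Pearson and Fisher tests refer the observed table to a distribution in which every patient is independent. That fails here for two reasons that pull in opposite directions.

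- **Clustering.** Patients in one practice resemble each other, so group proportions vary more than the test allows. It then rejects too often.
- **Matching.** Controls are chosen to resemble intervention patients, so matched characteristics differ less than independent samples would. The test then rejects too rarely.

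The p-value therefore has no fixed meaning from one row of the baseline table to the next. Categorical variables are also held to a different standard from continuous ones, whose mixed models can at least carry a practice effect.

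In a non-randomised study the evidence that the comparator is adequate matters, and the Discussion itself says that validity depends on the matched control group. Two things are exposed: the judgement on the matching, and the covariate set of the adjusted models. Because the article names these tests, this is a stated choice of method and not a detail left to a statistical analysis plan.

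**Working it through.** The plan states no error rate for the baseline tests, so there is no figure of its own to reproduce. Its stated 82% power concerns the ASE rate and plays no part here.

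**Inputs**
- From the Sample size calculation: 20 practices per arm and m = 112 patients per practice.
- From Effectiveness evaluation: two-sided 5% level.
- Assumed: the ICC (ρ) of a baseline characteristic. The value 0.01 is borrowed from the ASE power calculation as an illustration; 0.001 to 0.05 is shown as a range.

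**1. Unmatched two-category variable, practices of 112 in both arms**

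Design effect: DE = 1 + (m − 1)ρ. Actual size of the nominal 5% test: 2[1 − Φ(1.96/√DE)].

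At ρ = 0.01, DE = 1 + 111 × 0.01 = 2.11, and 1.96/√2.11 = 1.349, so the size is 17.7%. Beta-binomial simulation with prevalences from 0.1 to 0.5 gives 17.5–18.0%.

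| ρ | DE | actual size |
|---|---|---|
| 0 | 1.00 | 5.0% |
| 0.001 | 1.11 | 6.3% |
| 0.005 | 1.56 | 11.6% |
| 0.01 | 2.11 | 17.7% |
| 0.02 | 3.22 | 27.5% |
| 0.05 | 6.55 | 44.4% |

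With 10% patient dropout (m = 101) at ρ = 0.01, DE = 2.00 and the size is 16.6%.

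**2. Unmatched variable with more categories, ρ = 0.01**

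The sentence assigns binary variables to logistic models, so variables with three or more categories are the more relevant case for the quoted tests. The size is P(χ² on k − 1 df > critical value/2.11).

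| categories | critical value | divided by 2.11 | actual size |
|---|---|---|---|
| 3 | 5.99 | 2.84 | 24% |
| 4 | 7.81 | 3.70 | 30% |
| 5 | 9.49 | 4.50 | 34% |

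**3. Controls spread thinly, ρ = 0.01**

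The matching method is still open, so controls may come from many practices. With one control per practice the control-arm DE is 1. The average is (2.11 + 1)/2 = 1.555, and the two-category size is 11.6%. With five per practice it is (2.11 + 1.04)/2 = 1.575, giving 11.8%.

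**4. Variable used in the matching, ρ = 0.01**

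Suppose a share c of controls have the same category as their matched patient by construction, and the rest follow their own practice of 112. Only the share u = 1 − c contributes to the difference. The true variance relative to what the test assumes is about u[1 + (um − 1)ρ], and this replaces DE in the step 1 formula.

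| c | variance ratio | actual size | simulation |
|---|---|---|---|
| 25% | 0.75 × 1.83 = 1.37 | 9.4% | about 10% |
| 50% | 0.50 × 1.55 = 0.78 | 2.6% | about 2% |
| 75% | 0.25 × 1.27 = 0.32 | 0.05% | about 0% |

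So a variable that is only half matched is already tested below the nominal level.

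**The case against.** The strongest reply has four parts.

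**No single figure is supported.** A reader might infer that the baseline tests raise false alarms 18% of the time at the plan's own ICC. The documents do not support that. The 0.01 is the ICC for the ASE rate. The 18% is a two-category result, and it needs controls in clusters of 112 and no matching on the variable. This part stands, so the figure is given only as an illustration with a range.

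**Many tested variables will be matched.** The Matching and Control group sections list age, sex, diagnosis, comorbidities and prior ASE. A reader might infer that a sound match will regularly be declared a failure. For these variables the error can run the other way. This stands as a correction of direction, but a test that conceals imbalance is no better suited to checking a match.

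**Balance is a property of the realised sample.** If the groups differ because their practices differ, the difference is real. This also stands. It argues against significance tests as the yardstick, and it shows why adding a practice random intercept is not a sufficient remedy.

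**The consequence is limited.** The Matching section chooses the method by the balance achieved and names no p-value, and no rule rejects a match on a significant baseline test. This stands. The Effectiveness evaluation section nevertheless gives this comparison the purpose of assessing the matching and feeds its results into covariate selection.

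Two further inferences go too far. The article does not say that the logistic models lack a practice term; it is silent. And the abstract's sentence on clustering is a summary that the outcome models do honour, so the baseline tests fall short of it without making it false.

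**Conclusion.** The concern holds in a limited form. The named chi-square and Fisher tests disregard both practice clustering and matching, and the same sentence treats continuous variables differently. The resulting p-values are miscalibrated in a direction that depends on the variable. For unmatched two-category variables with 112 patients per practice, the actual size runs from about 6% to 44% as the assumed ICC goes from 0.001 to 0.05. At 0.01 it is about 18%, or about 12% if controls are dispersed. With three to five categories at 0.01 it is 24–34%. For closely matched variables it falls well below 5%.

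A reader might conclude that the primary result is compromised. It is not directly affected: the ASE model nests patients in practices, with cluster-robust standard errors as a check. The harm is confined to the balance evidence and to covariate choice. This should be corrected, but it does not threaten the trial.

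**What to change.** In the Effectiveness evaluation section:

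1. Replace the baseline significance tests with standardised differences for all patient-level variables, whatever their type. These describe the matched sample and need no independence assumption.
2. Compare practice-level variables on one record per practice.
3. Choose adjustment covariates by prognostic relevance and residual standardised difference, not by these p-values.
4. If tests are kept, use models that account for practice, and for matched sets where the matching method creates them, for binary and categorical variables as well as continuous ones. A practice random intercept alone would still ignore the matching.

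The cost is the p-value column of the baseline table or, under item 4, a little more modelling. No new data are needed, and the analysis phase starts only in October 2027.

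### The primary model takes its covariates from an initial analysis of the matched sample and does not fix the pre-period ASE count, which a test of group differences would tend to miss

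*Protocol article*

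**What the plan says.** The section Sample size calculation describes a parallel cluster design and adds: "The design includes 12 months of pre- and 12 months of post-intervention observation". Its inputs are that "a baseline rate of 0.20 ASE per patient per year is assumed" and that "a conservative effect size of 15% is applied". It concludes that "the study achieves a statistical power of 82% to detect a 15% reduction in ASE rates". It gives no correlation between the two periods.

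The subsection Matching lists prior ASE, with age and sex, as examples of patient-level matching variables. Practice type and size are the practice-level examples, and regional indicators are considered. The matching method is still open.

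The subsection Effectiveness evaluation then runs three steps:

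1. The intervention group (IG) is compared with the matched control group (CG) at baseline. The comparison has two aims: to check the matching, and to find possible drivers of the endpoints. For this, "The significance of the differences will be tested using linear mixed models for continuous variables with normal distribution"; logistic models, chi-square tests and Fisher's test serve the other variable types.
2. Next, "the rate of ASE in the IG and CG will be analyzed using multi-level regression models with patients nested within practices".
3. Finally, "Relevant covariates identified in the initial analyses will be included in adjusted regression models". Secondary endpoints follow the same selection rule.

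No pre-period ASE term and no contrast of period by group is named for the primary model.

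**The concern.** This is a non-randomised comparison, so the adjusted model carries much of the causal claim. Its covariate set should be fixed before outcomes are seen. The article instead states a rule that reads the set off the matched analysis sample, and the only tests it describes for that step compare IG with CG.

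Such a test is a poor guide. Its p-value depends on sample size as well as on imbalance, and it says nothing about whether a variable predicts the outcome. It is least useful for a variable used in matching: the better the matching on prior ASE, the smaller the group difference and the less likely the test is to flag it. Balance does not make the variable redundant. It can still explain outcome variation, and the standard error of a model without it does not credit what matching removed.

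At stake are precision, protection against residual imbalance in prior ASE, and the nominal meaning of the p-value when the model is chosen on the data it is fitted to.

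**Working it through.** **Inputs from the article (Sample size calculation).** Control rate 0.20 per patient-year; 15% reduction, so 0.17; 20 practices per arm with m = 112, so n = 2,240 per arm; ICC 0.01; two-sided 5%; stated power 82%.

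**Assumptions (not in the article).** Cluster autocorrelation (CAC) 0.8-1.0. Negative binomial overdispersion k = 0 (Poisson) or 2. Patient-level autocorrelation IAC = 0.2k/(1 + 0.2k), which is 0 for k = 0 and 0.4/1.4 = 0.29 for k = 2.

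**1. The plan's own figure, post-period only.**
- Design effect = 1 + 111 × 0.01 = 2.11.
- Variance = (0.20 + 0.17)/2,240 × 2.11 = 0.000349, so SE = 0.0187.
- z = 0.03/0.0187 = 1.61, and power = Φ(1.61 − 1.96) = 36%. Treating the outcome as binary gives 43%.

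The 82% is not reproduced. With the pre-period as a covariate, the variance is multiplied by 1 − r², where r is the pre/post correlation of practice means. At r = 0.83, 1 − r² = 0.311, SE = 0.0104, z = 2.88 and power = Φ(0.92) = 82%. The binary version needs r of about 0.79. So, with the stated alpha and ICC, 82% is within reach only if the pre-period enters the analysis with a strong correlation. Because r is not given, this does not show that 82% is wrong.

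**2. Gain if the arms are not closely matched on prior ASE.**

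r = [m × ICC × CAC + (1 − ICC) × IAC] / 2.11

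| k | CAC | r | 1 − r² | Variance cut |
|---|---|---|---|---|
| 0 | 0.8 | 0.896/2.11 = 0.42 | 0.82 | 18% |
| 0 | 1.0 | 1.12/2.11 = 0.53 | 0.72 | 28% |
| 2 | 0.8 | (0.896 + 0.283)/2.11 = 0.56 | 0.69 | 31% |
| 2 | 1.0 | (1.12 + 0.283)/2.11 = 0.66 | 0.56 | 44% |

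For k = 0, power goes from 36% to 43-47%. For k = 2, the per-patient variances sum to 0.20 × 1.40 + 0.17 × 1.34 = 0.508. SE is then √(0.508/2,240 × 2.11) = 0.0219 and power 28%, rising to 38-45%. Simulation of unmatched arms gave similar variance ratios: 0.82-0.72 for k = 0 and 0.70-0.61 for k = 2.

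**3. Gain if controls are matched closely on prior ASE.** The formula in step 2 assumes that the arms differ by chance in prior ASE, which close matching removes. The same scenarios were therefore simulated with each control matched exactly on prior count, in paired practices (an assumption, since the method is open):
- The variance ratio, adjusted to unadjusted, is about 0.98-1.00.
- Power for k = 0 goes from about 0.33-0.35 to 0.36-0.37, a gain of 2-3 points.
- Power for k = 2 goes from about 0.24 to 0.32-0.33. A separate simulation gave 0.26-0.27 to 0.33-0.34. Together that is 7-9 points.

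The estimate barely moves, so these gains come from the standard error. The unadjusted analysis charges the full spread of practice means, including the part that matching has already removed from the comparison.

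**The case against.** The strongest reply has four parts.

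**The rule may not be a p-value screen.** No entry threshold is stated, and looking for drivers of the endpoints may mean association with the outcome, in which case prior ASE could well be picked up. This stands against the inference that covariates enter only through tests of group differences. It does not rescue the rule, because a set chosen by outcome association is also chosen on the analysis data.

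**Matching already uses prior ASE.** This stands, and it limits the point in three ways. A reader might take the 18-44% variance cut as the expected gain, but step 3 shows that it applies only when matching on prior ASE is loose. A reader might also say that matching makes the group difference non-significant by construction. The method is undecided, so the supported claim is that a test would tend not to flag it. Nor is control of stable practice differences left to chance: practice type and size are matched, regional indicators are considered, and the Discussion acknowledges selection of volunteer practices and residual differences.

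**The analysis plan is not shown.** An exact covariate list may sit there, and its absence from the article is no finding. What remains is the rule that the article does state.

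**Adding many terms has a price.** With about 40 practices, a long list of practice-level covariates uses up degrees of freedom. This stands and shapes the fix.

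**Conclusion.** The point holds as a free improvement. The article states a data-driven covariate rule for the primary model, describes only IG-versus-CG significance tests for that step, and fixes no pre-period ASE term although its design includes a 12-month pre-period.

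The size depends on how close the matching is. It ranges from a variance reduction of up to about 18-44% under loose matching to almost none under close matching. In the latter case what remains is a better-calibrated standard error, 2-3 points of power (k = 0) to 7-9 points (k = 2), and protection against residual imbalance. All of this rests on the assumed CAC and k. That prior ASE is a strong predictor is likely but not documented; at k = 0 it predicts only through the practice.

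A reader might infer that the fix would deliver the stated 82%. It does not: across the scenarios above, adjusted power stays below 50%. The basis of the 82% is a separate question.

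**What to change.** In Effectiveness evaluation, and in the analysis plan if it does not already do so:

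- Pre-specify the primary model as a count mixed model with patients nested in practices. Include the patient's 12-month pre-period ASE count and the main matching variables as covariates, whatever their p-values.
- Keep practice-level terms few, for example the practice's pre-period ASE rate, given about 40 practices.
- Judge balance after matching by standardised mean differences. Drop significance tests for judging balance and for choosing covariates.
- Apply the same fixed-covariate principle to the secondary endpoints, which now inherit the selection rule.

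The cost is wording. The claims data start on 1 January 2024, two years before the first enrolment, so the pre-period count is available for every patient with continuous data. Analysis begins only in October 2027, so the model can still be fixed before outcomes are examined. If the analysis plan already lists these covariates, only the article's sentence needs correcting.

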### Health economic evaluation

The health economic evaluation will first assess the costs of ambulatory care within the IG from an ambulatory care payer perspective and relate these costs to the number of ASE. Results will be presented as incremental cost-effectiveness ratios (ICERs). Costs considered will include both project-specific costs (e.g., employment of the PNs and the PRIMA reimbursement model) and ambulatory healthcare expenditures reimbursed by SHI funds. Resource utilization will be derived from routine data and valued using standardized unit costs. Sensitivity analyses will be conducted to assess the robustness of the results, while statistical uncertainty of the ICERs will be estimated using cost-effectiveness acceptability curves. In addition to the SHI physician perspective, a separate analysis will be conducted from the perspective of participating general practices. This analysis will compare implementation-related costs (e.g., employment of PNs) with additional revenues generated through newly established reimbursement codes in order to assess the economic feasibility of the NCM.

For the population insured by AOK BW, total healthcare costs from the sickness fund perspective will be analyzed. In addition to ambulatory care costs, this analysis will include further sectors of care, such as inpatient care, medical aids and appliances, pharmaceuticals, rehabilitation services, and sickness benefits, where available in the routine data. These costs will subsequently be related to the number of ASE using ICERs. Additional sensitivity analyses and cost-effectiveness acceptability curves will be used to assess uncertainty in the economic evaluation.

All statistical analyses will be conducted in R (latest version; R Foundation for Statistical Computing) using RStudio or comparable tools, according to predefined standard operating procedures (SOPs).

